## Abstract

**Background:**

There is a marked lack of evidence on the optimal prevention of ischaemic stroke and other thromboembolic events in patients with non-valvular atrial fibrillation and a recent intracerebral haemorrhage during treatment with oral anticoagulation. These patients are currently treated with oral anticoagulants, antiplatelet drugs, or no antithrombotic treatment, depending on personal and institutional preferences.

Compared with warfarin, the direct oral anticoagulant apixaban reduces the risk of stroke or systemic embolism, intracranial haemorrhage, and case fatality in patients with atrial fibrillation. Compared with aspirin, apixaban reduces the risk of stroke or systemic embolism in patients with atrial fibrillation, and has a similar risk of intracerebral haemorrhage. Novel oral anticoagulants have not been evaluated in patients with atrial fibrillation and a recent intracerebral haemorrhage.

To inform a phase III trial, the phase II Apixaban versus Antiplatelet drugs or no antithrombotic drugs after anticoagulation-associated intraCerebral HaEmorrhage in patients with Atrial Fibrillation (APACHE-AF) trial aims to obtain estimates of the rates of vascular death or non-fatal stroke in patients with atrial fibrillation and a recent anticoagulation-associated intracerebral haemorrhage treated with apixaban and in those in whom oral anticoagulation is avoided.

**Methods/Design:**

APACHE-AF is a phase II, multicentre, open-label, parallel-group, randomised clinical trial with masked outcome assessment. One hundred adults with a history of atrial fibrillation and a recent intracerebral haemorrhage during treatment with anticoagulation in whom clinical equipoise exists on the optimal stroke prevention strategy will be enrolled in 14 hospitals in The Netherlands.

These patients will be randomly assigned in a 1:1 ratio to either apixaban or to avoiding oral anticoagulation. Patients in the control group may be treated with antiplatelet drugs at the discretion of the treating physician. The primary outcome is the composite of vascular death or non-fatal stroke during follow-up. We aim to include 100 patients in 2.5 years. All patients will be followed-up for the duration of the study, but at least for 1 year. Recruitment commenced in September 2014 and is ongoing. This trial is funded by the Dutch Heart Foundation (2012 T077) and ZonMW (015008048).

**Trial registration:**

NTR4526 (16 April 2014).

**Electronic supplementary material:**

The online version of this article (doi:10.1186/s13063-015-0898-4) contains supplementary material, which is available to authorized users.

## Background

Stroke is a major cause of death and disability and is associated with high healthcare expenditure [1, 2]. About 80 % of strokes are ischaemic, 15 % intracerebral haemorrhage (ICH), and 5 % subarachnoid haemorrhage [3].

Cardioembolism, most often caused by non-valvular atrial fibrillation (AF), accounts for 13 to 27 % [4, 5] of ischaemic strokes. The average annual risk of ischaemic stroke in patients with AF not treated with antithrombotic drugs is 4.5 % [6]. The risk of ischaemic stroke can be estimated with the CHA_2_DS_2_-VASc score [7]. The annual thromboembolic event rate increases from 2.2 % with a CHA_2_DS_2_-VASc score of 2 to 15.2 % with the maximum score of 9 [8]. In patients with AF and a CHA_2_DS_2_-VASc score ≥ 1, treatment with an oral anticoagulant (OAC) is recommended [9, 10]. Traditionally, vitamin K antagonists (VKA) have been the first choice for prevention of thromboembolic events in these patients. While VKA therapy decreases the risk of ischaemic stroke, it increases the risk of ICH, the most devastating complication of OAC therapy. The risk of ICH in patients with AF treated with vitamin K antagonists is 0.3 to 3 % per year, and increases with increasing age [11–14]. This complication leads to death in 45 % of cases, and only 17 % of patients recover without disability [15].

In patients with AF who are unsuitable for VKA therapy because of poor compliance or allergy, or who are unwilling to receive this therapy, antiplatelet drugs (APDs, e.g. acetylsalicylic acid, clopidogrel) may be considered [9, 10]. However, antiplatelet treatment only results in a modest reduction in the risk of ischaemic stroke [16] and increases the risk of major bleeding as compared to no antithrombotic therapy (incidence rate ratio 1.55; 95 % confidence interval (CI), 1.48–1.63)) [17].

In patients with AF who survive an anticoagulation-related ICH, a longstanding and pressing clinical dilemma is whether or not to resume treatment with oral anticoagulation to prevent ischaemic stroke and other future thrombotic and embolic complications [18, 19]. Randomised trials have not been performed and reliable estimates of the risk of recurrent ICH or ischaemic stroke after resumption of antithrombotic drugs on the one hand, or permanent discontinuation of these drugs on the other, are lacking [20].

Patients with AF on warfarin who survive an ICH have a higher event rate for the combination of ischaemic stroke, systemic embolism or transient ischaemic attack in the 2 years following the ICH compared with AF patients on warfarin who did not experience an ICH (event rate ratio, 5.40 (95 % CI 4.04 to 7.22) [21].

In retrospective studies of small patient cohorts, the annual risk of recurrent ICH after resumption of VKAs varied between 2.5 and 20 % and that of ischaemic stroke between 0 and 33 % [22–26]. In patients in whom VKAs were discontinued permanently, the risk of ICH varied between 0 and 9 % and the risk of ischaemic stroke between 10 and 48 % [22–26].

In small observational studies of patients who survived an ICH – regardless of whether this occurred during the use of a VKA – no difference was found in the risk of recurrent ICH between patients treated with acetylsalicylic acid after the initial ICH and those who used no antithrombotic drugs [25, 27–29], with an annual risk of recurrent ICH between 2.3 and 8.2 % [27, 29]. The annual risk of ischaemic stroke in these patients varied between 1.3 and 9.4 %.

The above-mentioned estimates for the risk of ischaemic stroke or recurrent ICH during treatment with VKA or APD are not reliable because of selection bias, the inclusion of patients with different indications for the use of antithrombotic drugs, and variation in target international normalised ratios (INRs). In addition, estimates varied widely between studies and had wide CIs because of the small numbers of patients included.

The aforementioned information illustrates that there is a need for evidence-based recommendations for the prevention of stroke and other thromboembolic complications in survivors of anticoagulation-related ICH [30, 31]. Currently, patients are treated – based on ‘expert opinion’ – with OAC, APDs, or no antithrombotic medication at all, resulting in marked practice variation [32].

In the past few years, novel, direct anticoagulant drugs (DOACs) have been introduced in clinical practice. These drugs reduce coagulation by inhibition of factor Xa (rivaroxaban, apixaban and edoxaban) or factor IIa (dabigatran), resulting in a reduced thrombin generation, diminished enzymatic conversion of fibrinogen to fibrin and, thus, less efficient clot formation.

In the randomised Apixaban for Reduction in Stroke and Other Thromboembolic Events in Atrial Fibrillation (ARISTOTLE) study, the oral factor Xa inhibitor apixaban at a dose of 5 mg twice daily was more effective than warfarin (target INR, 2.0 to 3.0) in preventing stroke or systemic thromboembolism in patients with AF: hazard ratio, 0.79; 95 % CI, 0.66 to 0.95; *P* < 0.001 for non-inferiority; *P* = 0.01 for superiority. Patients treated with apixaban less often had an ICH (hazard ratio, 0.51; 95 % CI, 0.35 to 0.75; *P* < 0.001) than patients treated with warfarin [33]. These beneficial effects were seen throughout different times in therapeutic range (TTR) ranges [34].

Of the DOACs, only apixaban has been compared with acetylsalicylic acid in a randomised controlled trial in patients with AF. In the trial Apixaban Versus Acetylsalicylic Acid to Prevent Stroke in Atrial Fibrillation Patients Who Have Failed or Are Unsuitable for Vitamin K Antagonist Treatment (AVERROES), patients with AF who were treated with apixaban 5 mg twice daily had a lower risk of stroke or systemic embolism than patients treated with acetylsalicylic acid at a dose of 81 to 324 mg per day (hazard ratio 0.45; 95 % CI 0.32 to 0.62; *P* < 0.001), whereas the rates of ICH in the 2 groups were similar [35].

In phase III randomised trials comparing other DOACs with warfarin in patients with AF, these were non-inferior to warfarin in the prevention of stroke and systemic embolism and were associated with a reduced risk of intracranial bleeding [36–38].

In a meta-analysis of phase III randomised trials of patients with AF who were randomised to receive DOACs or warfarin, the DOACs had a favourable risk-benefit profile, with significant reductions in stroke, intracranial haemorrhage, and mortality, and with a similar major bleeding risk as for warfarin, but an increased risk of gastrointestinal bleeding. The relative efficacy and safety of DOACs was consistent across a wide range of patients [39].

The DOACs have not been compared against each other in clinical trials. A meta-analysis using a Baysian random effects model suggested that the risk reductions for ICH as compared to warfarin are similar [40]. There are no clinical trials testing the effect of a DOAC in patients with AF and a recent oral anticoagulant-associated intracerebral haemorrhage (OAC-ICH).

We hypothesise that in patients with AF who survived an anticoagulation-associated ICH, treatment with apixaban may be the best long-term alternative for the prevention of recurrent stroke and systemic thromboembolism. To test this hypothesis, a conclusive phase III, randomised clinical trial comparing the long-term effects of apixaban with those of APDs or no antithrombotic treatment in these patients is required. Before such a trial can commence, a phase II trial is needed to obtain reliable estimates of the rates of vascular death or non-fatal stroke for both strategies in patients with AF and a recent anticoagulation-associated ICH. As a secondary objective, we aim to compare the rates of all-cause death, vascular death, stroke, ischaemic stroke, recurrent ICH, other major haemorrhage, systemic embolism, myocardial infarction, and functional outcome between patients treated with apixaban and those in whom anticoagulation is avoided.

### Rationale for study treatment

The treating physician will decide on any of the treatment regimens in the comparator group. This design is based on the lack of evidence that any of the treatment options has a more favourable risk-benefit ratio in this population than others [18, 32, 41, 42].

Allowing variable treatment regimens enables us to include patients with or without a medical history of atherosclerotic disease, which could warrant the use of APDs. The choice for these treatment options in the comparator arm enables us to achieve close similarity with current clinical practice and include as many eligible patients as possible to answer the research question.

The physician can include other indications for APDs (e.g., a history of myocardial infarction) in the decision on the treatment in the comparator arm.

Treatment with any of the drugs in the study can commence anywhere between 7 and 90 days after the ICH, at the discretion of the treating physician. There are reports suggesting that VKAs can be resumed after 3 days [43], whereas others recommend resumption of antithrombotic drugs anywhere between 70 and 210 days, if at all [24]. In the absence of evidence on the optimal timing of the resumption of antithrombotic drugs after ICH, we chose this interval as it reflects clinical practice.

## Methods/Design

### Overview

APACHE-AF (Fig. 1, http://www.apache-af.nl) is a phase II, randomised, open-label, parallel-group, multicentre clinical trial with masked outcome assessment (PROBE design [44]), comparing apixaban and avoiding anticoagulation in patients with AF and a recent anticoagulation-associated ICH. An adjudication committee blinded to treatment allocation will adjudicate outcomes.

**Fig. 1 Fig1:**
[figure not shown]
Trial logo

A total of 100 patients will be included in 7 academic and 8 regional hospitals in the Netherlands over a period of 2.5 years. Members of the various study committees are listed in Appendix 1. Follow-up will continue until 1 year after inclusion of the last patient. The total study period is expected to be 4 years. Patient recruitment has started in September 2014.

### Eligible patients

Patients with AF who recently had an ICH during the use of anticoagulation, in whom there is clinical equipoise regarding the optimal medical treatment for the prevention of stroke, are eligible for participation in this trial. The ICH should have occurred between 7 and 90 days prior to randomisation. The CHA_2_DS_2_-VASc score should be 3 or higher [8] and the score on the modified Rankin Scale (mRS) [45], as a measure for disability, 4 or lower. Detailed eligibility criteria are shown in Table 1.

**Table 1 Tab1:** Eligibility criteria

**Inclusion criteria**
Intracerebral haemorrhage (including isolated spontaneous intraventricular haemorrhage), documented with CT or MRI, during treatment with anticoagulation (VKA, any direct thrombin inhibitor, any factor Xa inhibitor, or (low-molecular-weight) heparin at a therapeutic dose)
The haemorrhage has occurred between 7 and 90 days before randomisation
Diagnosis of (paroxysmal) non-valvular AF, documented on electrocardiography
A CHA_2_DS_2_-VASc score ≥ 3
Score on the modified Rankin Scale (mRS) [45]
Equipoise regarding the optimal medical treatment for the prevention of stroke. The clinical equipoise should be self-reported by the attending neurologist after reviewing all relevant information available for the individual patient
Age ≥ 18 years
Written informed consent by the patient or by a legal representative
**Exclusion criteria**
Conditions other than AF for which the patient requires long-term anticoagulation
A different clinical indication for the use of an antiplatelet drug even if treated with apixaban, such as clopidogrel for recent coronary stenting
Mechanical prosthetic heart valve (biological prosthetic heart valves are allowed) or rheumatic mitral valve disease
Serious bleeding event in the previous 6 months, except for intracerebral haemorrhage^a^
High risk of bleeding (e.g. active peptic ulcer disease, a platelet count of < 100,000 per ml or haemoglobin level of < 6.2 mmol L^-1^ ischaemic stroke in the previous 7 days (patients are eligible thereafter), documented haemorrhagic tendencies, or blood dyscrasias)
Current alcohol or drug abuse
Life expectancy of less than 1 year
Severe renal insufficiency (a serum creatinine level of more than 221 μmol L^-1^ or a calculated creatinine clearance of < 15 ml per minute)
Alanine aminotransferase or aspartate aminotransferase level greater than twice the upper limit of the normal range or a total bilirubin more than 1.5 times the upper limit of the normal range, unless a benign causative factor (e.g. Gilbert’s syndrome) is known or identified
Allergy to apixaban
Use of strong cytochrome P450 3A4 (CYP3A4) and P-glycoprotein (P-gp) inhibitors (e.g. systemic azole-antimycotics such as ketoconazole or HIV protease inhibitors such as ritonavir)
Pregnancy or breastfeeding
Women of childbearing potential: any woman who has begun menstruation and is not postmenopausal or otherwise permanently unable to conceive. A postmenopausal woman is defined as a woman who is over the age of 45 and has not had a menstrual period for at least 12 months

^a^Serious bleeding event: see major extracranial haemorrhage and clinically relevant non-major bleeding in Table 3

*AF* atrial fibrillation, *CT* computed tomography, *MRI* magnetic resonance imaging, *VKA* vitamin K antagonist

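### The platelet cut-off in Table 1 is given per ml, a thousandfold below the value evidently meant, so the platelet example cannot work as printed

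*Protocol article*

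**What the plan says.** The protocol article's section on eligible patients refers the reader to Table 1 for the detailed criteria. In the exclusion half of that table, one row begins "High risk of bleeding (e.g. active peptic ulcer disease" and continues with further examples. One of them is a platelet limit, fewer than "100,000 per ml or haemoglobin level of" a stated value in mmol per litre. The row also lists a recent ischaemic stroke and ends with "documented haemorrhagic tendencies, or blood dyscrasias".

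Two limits on renal function appear lower in the same table: "a serum creatinine level of more than 221 μmol L^-1" and "a calculated creatinine clearance of < 15 ml per minute". No other section of the article gives a platelet limit.

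**The concern.** Platelet counts are ordinarily reported per microlitre or in units of 10^9/L. A limit of 100,000 is a recognisable cut-off per microlitre but not per millilitre, where it is far below any count that could serve for screening.

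This is the only numerical platelet limit in the eligibility table. The trial gives apixaban to patients who have recently had an intracerebral haemorrhage, and the section on ethical considerations accepts that apixaban or an antiplatelet drug probably raises the risk of recurrent or other major bleeding. If the printed limit were applied literally, a low platelet count would lead to exclusion only through the other parts of the row or through clinical judgement. The blood values listed under study parameters are haemoglobin, liver enzymes and creatinine, without platelets. On the article's own list, therefore, a wrongly admitted low count would not show up in the trial data, although the full protocol may collect it.

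**Working it through.** **Inputs.** The printed limit of 100,000 per ml comes from Table 1, exclusion criteria. The intended unit is not stated. The microlitre is assumed, because an ordinary platelet count is taken to be about 150 to 400 x 10^9/L.

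**Printed limit in standard units.**

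- 100,000 per ml x 1,000 ml/L = 1 x 10^8/L = 0.1 x 10^9/L
- 100,000 per ml / 1,000 microlitres per ml = 100 per microlitre

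**Limit evidently meant.**

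- 100,000 per microlitre x 10^6 microlitres/L = 1 x 10^11/L = 100 x 10^9/L

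**Ratio.** 100 / 0.1 = 1,000.

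**What the printed limit does to low counts.**

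| Count (x 10^9/L) | Count per ml | Multiple of the printed limit | Excluded by the printed limit? | Excluded by < 100 x 10^9/L? |
|---|---|---|---|---|
| 50 | 50,000,000 | 50,000,000 / 100,000 = 500 | No | Yes |
| 20 | 20,000,000 | 20,000,000 / 100,000 = 200 | No | Yes |
| 10 | 10,000,000 | 10,000,000 / 100,000 = 100 | No | Yes |

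Of the band from 0 to 100 x 10^9/L, the printed limit misses (100 - 0.1) / 100 = 99.9%. This is a share of the measurement scale, not of patients.

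**Could the unit be a fault of text extraction?** The micro sign is intact in the creatinine limit of the same table and in the dose-reduction footnote to Table 2. The unit ml is used correctly for creatinine clearance. The haemoglobin and creatinine concentrations are given per litre, and only the platelet count is given per ml. A micro sign lost in extraction is therefore unlikely, though not excluded.

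**How many patients could be concerned?** The documents give no frequency of low counts. If 0% to 5% of candidates had counts below 100 x 10^9/L (an assumption), then 100 x 0 = 0 to 100 x 0.05 = 5 of the 100 planned patients would fall in the band. That is the number before the other safeguards apply, not an estimate of wrong enrolments.

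**The case against.** The strongest reply is that nobody would be misled. A limit of 0.1 x 10^9/L is absurd as a screening value, so a clinician would see 100,000 and supply the right unit. The figure is also only an illustration: the exclusion is high bleeding risk itself, the row goes on to haemorrhagic tendencies and blood dyscrasias, and the attending neurologist must declare equipoise after reviewing the individual patient's information. Sites probably did not work from this article either, since it reports ethics approval in August 2014 and first inclusions in January 2015 as past events. Finally, Table 1 shows other signs of lost text: its modified Rankin line has no threshold, although the section on eligible patients gives one, and the bleeding row lacks a separator before the ischaemic stroke item. A typesetting cause is therefore possible.

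Most of this stands, and it limits the weight of the point. Clinicians would probably read the limit as intended, the other safeguards operate, and the number of patients wrongly enrolled is unknown and may well be zero. It does not remove the error. A threshold that works only when the reader replaces its unit is misstated, and nothing else in the article corrects it. A typesetting slip in the published table would also need correcting.

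**Conclusion.** The concern holds, as a minor point. The printed platelet limit is 0.1 x 10^9/L, against an evident intention of 100 x 10^9/L, an error of a factor of 1,000. The conversion is certain. That the microlitre was meant is an inference from the ordinary platelet range, and the sponsor should confirm it.

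The error is confined to one example in one exclusion row. It has no bearing on sample size, error rates, the interim boundaries or the analysis. Any effect on who was enrolled depends on the same slip being present in the full protocol or eligibility form, which are not shown, and on the other parts of the row and clinical judgement also failing.

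**What to change.** After the sponsor's clinicians confirm the threshold, replace the platelet example in Table 1 with < 100 x 10^9/L (equivalently, < 100,000 per microlitre), which also matches the per-litre style of the table's other concentrations. Check the full protocol and the electronic eligibility form for the same unit, and notify sites only if it appears there. The cost is a one-line correction and a check of two documents.

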#### Randomisation

Allocation to treatment groups will be based on randomisation through a web-based system. Treatment allocation will be stratified by the choice of treatment in the comparator arm (APD versus no APD) and will use a minimisation algorithm for age (≤75 years versus >75 years) and location of the haemorrhage (lobar versus non-lobar). This treatment allocation ensures that both treatment groups will be comparable with regard to the intended treatment in the comparator arm.

### Intervention

Patients will be randomised to treatment with apixaban 5 mg or 2.5 mg given orally twice daily, or to treatment with one or two oral APDs (acetylsalicylic acid, carbasalate calcium, clopidogrel, or dipyridamole) or no antithrombotic treatment at all, at the discretion of the treating physician. Details about the allowed treatments in both groups are shown in Table 2. Treatment will start immediately after randomisation and will continue for the duration of the study. If during the course of a patient’s participation in this study the treating physician feels that a particular antithrombotic drug is clearly indicated or contra-indicated, the choice of the antithrombotic drug may be changed.

**Table 2 Tab2:** Possible treatments in both trial arms

Arm 1: apixaban	Arm 2: avoid anticoagulation
Apixaban 5 mg twice daily	No antithrombotic treatment
Apixaban 2.5 mg twice daily^a^	Acetylsalicylic acid 80 mg once daily
	Carbasalate calcium 100 mg once daily
	Clopidogrel 75 mg once daily
	Acetylsalicylic acid 80 mg once daily and dipyridamole 200 mg twice daily
	Carbasalate calcium 100 mg once daily and dipyridamole 200 mg twice daily

^a^Reduced dose: the dose will be reduced if 2 of the 3 following criteria are met: age ≥ 80 years, body weight ≤ 60 kg or serum creatinine ≥133 μmol. If the creatinine clearance is below 30 ml per minute, the dose will also be reduced

Patients in both treatment groups will be treated according to the relevant guidelines for the prevention of stroke or systemic embolism.

